#### Control intervention group

All participants randomised to the control group receive the intervention usually provided in OPUS. There is no extra effort to control for the amount of clinician contact. As a meta-analysis by McGurk et al. argues, the need for such control is questionable, since trials of cognitive remediation have provided no supporting evidence that more clinician contact has an effect on improvements [14].

### Assessments

The first assessment occurs before randomisation, since information from the baseline assessment is used as stratification variables and to validate inclusion and exclusion criteria. At baseline, participants are administered the clinical version of WHO Present State Examination [54] and the Danish version of National Adult Reading Test [55,55], a widely used measure of pre-psychotic IQ. All other assessments are conducted in a fixed order at baseline, post-training, and at follow-up 10 months after inclusion, regardless of whether participants have followed the full training programme according to the intent-to-treat principle [i.e. [56]]:

• Functional capacity in two domains of daily life (finance and communication) assessed using the Danish version of UPSA-B [22,23].

• Neuropsychological tests of seven cognitive domains (see Table 1 Neuropsychological assessment tools used in the NEUROCOM trial.).

**Table 1 T1:** Neuropsychological assessment tools used in the NEUROCOM trial.

Domain of cognition	Tests
Speed of information processing	BACS Symbol Coding Category Fluency Trail Making A

Attention	Continuous Performance Test - Identical Pairs

Working memory	Wechsler Memory Scale-III Spatial Span Letter-Number Sequencing Trail Making B

Verbal learning and memory	Hopkin's Verbal Learning Test-Revised

Visual learning and memory	Brief Visuospatial Memory Test-Revised

Problem-solving	NAB Mazes Wisconsin Card Sorting Test, 64-card computerised version

Social cognition	Mayer-Salovey-Caruso Emotional Intelligence Test: Managing Emotions (MSCEIT)

Pre-psychotic IQ *	Danish National Adult Reading Test (DART) *

* Only assessed at baseline.

• Positive and negative symptoms evaluated with Positive and Negative Symptom Scale (PANSS, [57].

• Danish version of Rosenberg's Self-Esteem Scale [28,28].

• Assessment of occupational status and/or educational activities.

• Type and dose of antipsychotic medication (chlorpromazine equivalents).

• Participation in CBT or SST group treatment.

• Number of psychiatric hospitalisations.

• Sociodemographic variables: education, living status, economic conditions, relationships (partner, number of close friends) and number of children.

The primary outcome, UPSA-B, is a measure of functional capacity in which participants are asked to perform everyday tasks in two areas of functioning: the *Finance *subtest requires participants to count change, read a bill, and fill out a payment form to pay the bill. During the *Communication *subtest, participants are required to role-play an emergency call using an unplugged telephone as well as dial a number from memory and reschedule a doctor's appointment. The UPSA-B requires approximately 15 minutes to complete, and raw scores (range 0-20) are converted into scaled scores ranging from 0-100, with higher scores indicating better functional capacity.

### Danish adaptation of the UPSA-B

The Danish adaptation of the UPSA-B was performed by [name] with approval from the original author [name] and his co-workers [name] and [name] via email correspondence. In order to translate the original English version of the UPSA-B into Danish it is required to adapt stimuli to the Danish context. In the *Finance *subtest of counting change and paying a bill, the bill was modified to look like a Danish bill from the local electricity and gas supply, and all currency amounts were expressed in terms of the Danish krone (which is also a decimal currency system, like the U.S. dollar). The complexity of the amounts was retained by keeping an equivalent number of different coins and banknotes required for correct answers. Items in the *Communication *subtest (emergency call, phone numbers, doctor's appointment letter) were modified to be congruent with the local requirements. All modified items were kept at the approximately same level of difficulty as in the original version UPSA-B.

During the NEUROCOM trial period, a cross-national study of functional capacity in American and Swedish patients with schizophrenia has been published [58]. Performance on a Swedish translation of the UPSA-B was essentially identical to that of the American sample on the original English version, indicating that the UPSA-B measures performance-based abilities that are consistent across differences in culture. The authors suggest, that adaptation of the UPSA-B may well be practical in other Western cultures.

### Sample size estimation

The power of the study is set at 90%, i.e., beta = 0.1. Alfa is set at 0.05. The primary outcome UPSA-B consists of 1-point-items, and every item has a face validity of real-world significance, i.e. correctly performing an emergency call or correctly remembering a scheduled appointment. On that premise the minimal relevant difference (MIREDIF) is set at one point on UPSA-B total score (Mean = 17.63 points, SD = 1.66) [23,59]. We assumed the SD to be 1.66. To be able to detect a difference of one point on UPSA-B mean total score between the two groups, the required number of participants in each group is 31 or 62 in total. Estimated dropout of 45% necessitates recruitment of about 120 participants, 60 in each intervention group.

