#### Primary hypothesis

The effect on patients' functional capacity in daily life of a 16-week programme of computer-assisted CT integrated in OPUS is not different from OPUS alone [for a detailed description of the OPUS intervention see [21]], with regard to the primary response variable of everyday functional capacity as measured by a Danish adaptation of the brief version of the University of California San Diego Performance Skills Assessment (UPSA-B)[22,23].

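### The stated 31 per group does not give 90% power for a one-point difference between two groups; the stated inputs need 59 per group, and 31 to 33 give about 65–67% in an unadjusted comparison

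*Protocol article*

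**What the plan says.** All the inputs and the result stand in one paragraph of the protocol article, Methods, Sample size estimation.

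- Power: "The power of the study is set at 90%, i.e., beta = 0.1".
- Significance level: "Alfa is set at 0.05". Whether the test is one- or two-sided is not said. The primary hypothesis is a null without direction: the effect "is not different from OPUS alone [for a detailed description of the OPUS intervention".
- Effect: "the minimal relevant difference (MIREDIF) is set at one point on UPSA-B total score".
- Variability: "We assumed the SD to be 1.66". The same value is given beside a mean of 17.63 points, so it is the spread of scores and not of changes.
- Comparison: "To be able to detect a difference of one point on UPSA-B mean total score between the two groups". The Randomisation section gives 1:1 allocation.
- Result: "the required number of participants in each group is 31 or 62 in total".
- Inflation: "Estimated dropout of 45% necessitates recruitment of about 120 participants, 60 in each intervention group".

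The paragraph mentions no paired design, change score, baseline correlation or covariate gain. Baseline values enter only in the Statistical analysis section, as part of the mixed model, again without a correlation.

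**The concern.** A difference of one point with an SD of 1.66 is a standardised effect of 1/1.66 = 0.60. For two independent groups, 90% power at that effect takes close to 60 per group, so 31 looks like about half of what is needed. The recruitment target was built on the 62, so the shortfall carries through to the 120.

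This is the only power statement for the primary outcome. The article's Discussion itself foresees that the OPUS programme may leave little room for improvement, so a null result is a real possibility. Readers who trust the stated 10% type II error could take such a result as good evidence against a one-point benefit, when on the stated inputs an unadjusted comparison would miss that benefit about one time in three.

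**Working it through.** **Inputs** (all from Sample size estimation, except allocation, which is from Randomisation): difference δ = 1 point, SD σ = 1.66, α = 0.05, power 90%, allocation 1:1, dropout 45%, recruited 120. Assumption: two-sided test, in line with the non-directional hypothesis; the one-sided case is also shown. Normal quantiles: 1.960 and 1.2816, sum 3.2416.

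**1. Where 31 can come from.** One-sample or paired formula:

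n = (3.2416)² × 1.66² / 1² = 28.95, so 29 by the normal approximation.

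By the exact noncentral t, n = 30 gives 89.04% and n = 31 gives 90.06%. The smallest n reaching 90% is therefore 31, the protocol's figure. That this formula was used is an inference from the match.

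**2. The comparison described.** Two independent means:

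n per group = 2 × (3.2416)² × 1.66² / 1² = 57.9, so 58.

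By the exact t, 59 per group (power 90.06%), or 118 evaluable in total.

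**3. Other two-group variants** (exact t, per group):

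| Test | 80% power | 90% power |
|---|---|---|
| Two-sided | 45 | 59 |
| One-sided | 35 | 48 |

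None gives 31.

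**4. The dropout step.** 62 / 0.55 = 113, rounded up to about 120. This step is consistent with its own input; the error lies in the 62. Conversely, 120 × 0.55 = 66, or 33 per group. To end with 118 evaluable, 118 / 0.55 = 215 would have to be recruited.

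**5. Power for one point, unadjusted t-test:**

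| Per group | Two-sided | One-sided |
|---|---|---|
| 31 | 64.6% | 75.8% |
| 33 | 67.4% | 78.1% |
| 60 (no loss at all) | 90.5% | 94.9% |

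The normal approximation gives 66.0% at 31 and 68.7% at 33 (two-sided).

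**6. Detectable difference at 33 per group** (two-sided, exact t): 1.35 points for 90% power, 1.16 points for 80%.

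**7. Credit for baseline adjustment.** With a baseline–follow-up correlation r, the SD becomes 1.66 × √(1 − r²). The article gives no r, so a range is assumed. Two-sided power at 33 per group:

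| Assumed r | Adjusted SD | Power |
|---|---|---|
| 0.3 | 1.58 | 71% |
| 0.5 | 1.44 | 79% |
| 0.6 | 1.33 | 85% |
| 0.67 | 1.23 | 90% |

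**The case against.** Three arguments on the other side deserve weight.

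*The planned analysis is not an unadjusted t-test.* It is a repeated-measurements model with baseline UPSA-B and further covariates, and randomisation is stratified on baseline UPSA-B. Its power is therefore higher than 65–67%, by an amount the article does not let us determine. This stands as a limit on the power figure: 67% is what the printed inputs give, not the power of the final model. It does not rescue the sample size, because the calculation applies the SD of 1.66 directly to the between-group difference and claims no gain from adjustment. A correlation of about 0.67 would be needed and is nowhere assumed.

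*Dropout may not mean loss of outcome data.* Participants are to be assessed whether or not they complete training, and the analysis section distinguishes leaving the intervention from being lost to follow-up. If some of the 45% are still assessed, unadjusted power rises: 80.7% at 45 per group, 84.7% at 50, and 90.5% if all 60 are measured. So 67% is the low end of the unadjusted range. But the paragraph inflates 62 to about 120 for this dropout, so for planning it treats the 45% as lost. The closeness of 120 to the 118 needed leaves almost nothing for that loss.

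*The cause of the error is not documented.* This is correct. A smaller, unreported adjusted SD of about 1.2 would also give close to 90% power at 31 per group (89.8%). Nothing in the paragraph supports that reading, and the error does not depend on how it arose.

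A one-sided test does not help either: it needs 48 per group.

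**Conclusion.** The concern holds. On the protocol's own inputs the requirement is 59 per group (118 evaluable), nearly twice the stated 31. Two-sided power for one point is 64.6% at 31 per group and 67.4% at 33, against the 90% claimed.

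The 67% rests on a two-sided unadjusted comparison at a single time point, SD 1.66, and no outcome data from the 45% who drop out. Relaxing the second or third of these raises power by an amount the article does not fix. The mismatch between the printed inputs and the printed sample size rests on none of the assumptions about dropout or baseline adjustment. It is an error in a stated result, not a detail left to a fuller document.

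**What to change.** Rewrite the sample size paragraph so that inputs and result agree:

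- State that the test is two-sided, and that 90% power for one point with SD 1.66 needs 59 per group, 118 evaluable.
- State what 120 randomised with 45% dropout gives: about 33 per group, with about 67% power for one point, or 90% power for 1.35 points.
- If the baseline-adjusted model is the planning basis, give the assumed baseline–follow-up correlation and the resulting power (for example 79% at r = 0.5).
- If part of the 45% is expected to supply outcome data, say how many and base the power on that number.

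The 90% figure should not be carried into the results report unless one of these stated assumptions supports it. The cost is one corrected paragraph and a less favourable power statement. Design and recruitment stay as they are.

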### Ethical considerations and informed consent

The NEUROCOM trial has been approved by the Danish Ethics Committee (KF 01 300017) and the Danish Data Protection Agency, and the trial has been registered at http://www.clinicaltrials.gov (NCT00472862) before inclusion of the first participant. The interventions and methods of investigation involve no known physical or mental risks. Participation is voluntary and written informed consent is obtained. All participants are informed both verbally and in written form that they can withdraw from the trial at any time, without it having any consequences for their continued treatment.

### Statistical analysis

Continuous outcome measures will be analysed with repeated measurements in a mixed-effects model and performed using SPSS 17.0. Logistic regression analyses will be applied with binary outcome measures. Dosage of antipsychotic medication (in chlorpromazine equivalents) will be included as a covariate variable in the analyses. Dropout analysis will be carried out, comparing baseline values for participants who drop out of intervention with those who follow the entire intervention. Baseline values of measures will be included in the analyses whenever possible.

Data sets on non-completing participants will be included in the data analyses on an intention-to-treat basis. In case of non-existent outcome measures (withdrawal, dropout, lost to follow-up), the pattern of missing data and the assumption of missing data at random (MAR) will be explored. If data distribution is skewed, repeated-measurements analyses will be performed.

The primary outcome measure, performance on UPSA-B, will be analysed, like other continuous outcome measures, in a repeated-measurements model with unstructured variance matrix. This approach assumes that the distribution of missing data can be estimated from the information from previous interviews and from information about other patients in the database. The condition for using this method is the assumption that data are missing at random when taking into consideration the information extracted from baseline interviews and information about the other patients in the database. In this model, baseline values of the scales are included [60,61]. Variables included as covariates will be site (Aarhus/Copenhagen), level of education, pre-psychotic IQ (DART), baseline values of secondary verbal memory, and the baseline values of variables that differ significantly in dropout analyses.

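### The dropout analysis is defined by leaving the intervention rather than by a missing UPSA-B, and its significance screen is a poor way to add covariates to the primary model

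*Protocol article*

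**What the plan says.** Five statements in the protocol article bear on this point.

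- **The comparison.** Statistical analysis defines the dropout analysis by completion of the intervention: "Dropout analysis will be carried out, comparing baseline values for participants who drop out of intervention with those who follow the entire intervention".
- **Its use.** The covariates of the primary repeated-measurements model end with "the baseline values of variables that differ significantly in dropout analyses".
- **Follow-up after stopping.** Under Assessments, the post-training and 10-month assessments take place "regardless of whether participants have followed the full training programme according to the intent-to-treat principle". Statistical analysis adds: "Data sets on non-completing participants will be included in the data analyses on an intention-to-treat basis".
- **The missing-data assumption.** The primary model is valid on condition that "data are missing at random when taking into consideration the information extracted from baseline interviews" and the information about the other patients. Where outcome measures do not exist, "the pattern of missing data and the assumption of missing data at random (MAR) will be explored".
- **Terms fixed in advance.** "Variables included as covariates will be site (Aarhus/Copenhagen), level of education, pre-psychotic IQ (DART), baseline values of secondary verbal memory". On the outcome itself: "In this model, baseline values of the scales are included". Antipsychotic dose in chlorpromazine equivalents is named earlier in the section as a covariate.

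**The concern.** MAR is a statement about which UPSA-B values are missing. It becomes more plausible when the model conditions on baseline variables that predict both a missing assessment and the UPSA-B score. The one rule that adds variables to the model from the data looks for predictors of something else, namely leaving the intervention.

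Under the protocol's own follow-up rule the two events can separate in both directions. Someone who stops training but attends both visits counts as a dropout with no missing outcome. Someone who finishes training but misses the 10-month visit counts as a completer with one. In the control arm, which receives usual OPUS and has no 16-week course, it is also unclear what following the entire intervention means.

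The rule then selects by p-value. At this sample size such a screen often passes over moderate predictors, sometimes admits chance ones, and leaves part of the primary model's covariate set unknown until dropout has been observed. Sample size estimation allows for 45% dropout, so the missing-data assumption may carry considerable weight in the primary result.

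**Working it through.** The plan gives no figure for the performance of the dropout screen, so there is none to reproduce. The check is of the wording first, then of how such a screen behaves.

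**1. Is the screened event the same as a missing outcome?** No. The definition contrasts those who leave the intervention with those who complete it. Assessments keeps both groups under assessment, and Statistical analysis keeps non-completers in the analysis.

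**2. Power of the significance screen.**

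Inputs: 120 participants and 45% dropout (Sample size estimation); two-sided 5% level (alpha 0.05 is stated, two-sided is assumed). The 45% is a sample-size allowance; using it as the share who stop the intervention is an assumption.

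- Group sizes: 0.45 × 120 = 54 stoppers, 120 − 54 = 66 completers.
- Two-sample t test with noncentrality d × √(54 × 66 / 120) = d × 5.45 and 118 degrees of freedom.

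| Baseline difference d (SD) | Noncentrality | Power to flag it |
|---|---|---|
| 0.2 | 1.09 | 19% |
| 0.3 | 1.63 | 37% |
| 0.4 | 2.18 | 58% |
| 0.5 | 2.72 | 77% |

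If only the training arm could be classified (27 against 33, a further assumption), the four powers would be 12%, 21%, 33% and 47%.

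**3. Chance inclusions.** The protocol does not say how many variables are screened. For k independent variables with no true difference, the chance of at least one inclusion is 1 − 0.95^k:

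- k = 10: 1 − 0.95^10 = 40%, with 0.5 inclusions expected.
- k = 20: 1 − 0.95^20 = 64%, with 1 inclusion expected.

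**4. Cost of screening on the wrong event (illustration).** Assume that 45% stop, 45% of outcomes are missing, and a baseline variable differs by 0.5 SD between missing and observed and is related to stopping only through missingness. Let a be the share of stoppers with a missing outcome. The share b among completers is then (0.45 − 0.45a) / 0.55, and the difference visible between stoppers and completers is 0.5 × (a − b).

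| a | b | Visible difference (SD) | Power, planned comparison | Power, missing vs observed |
|---|---|---|---|---|
| 1.0 | 0 | 0.50 | 77% | 77% |
| 0.8 | 0.164 | 0.318 | 41% | 77% |
| 0.6 | 0.327 | 0.136 | 11% | 77% |

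The loss depends wholly on how far the two events overlap, which the protocol does not state.

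**5. What a missed variable could do to the result (illustration).** Suppose the omitted variable differs by 0.3 to 0.5 SD between missing and observed and has a partial correlation of 0.3 to 0.5 with UPSA-B given the terms already in the model (assumed). With 45% missing, an arm's observed mean shifts by 0.45 × gap × correlation:

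- Low end: 0.45 × 0.3 × 0.3 = 0.04 SD, times the assumed SD of 1.66 = 0.07 points.
- High end: 0.45 × 0.5 × 0.5 = 0.11 SD, times 1.66 = 0.19 points.

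If the arms behave alike, the shift cancels in the treatment comparison. In the extreme case of opposite directions it doubles, to 0.13 to 0.37 points, against a minimal relevant difference of 1 point.

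**The case against.** The strongest reply is that the section contains more than the dropout comparison. Where outcome measures are missing, it separately plans to explore the pattern and the MAR assumption. It also fixes a substantial core of covariates whatever their p-values, together with baseline scale values and antipsychotic dose. The significance rule only supplements that core. This stands, and it limits the harm.

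Several further points also stand in whole or in part.

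- The rule is stated in advance and selects on dropout, not on the outcome or the treatment effect. The Blinding section conceals allocation until the analyses are completed. Deliberate steering is therefore unlikely, although part of the covariate set still depends on post-randomisation data.
- One spurious baseline covariate costs about one degree of freedom and does not bias a randomised comparison.
- The section also lists dropout among the causes of missing outcomes, so the dropout analyses that feed the model may be meant more widely than the one defined. If so, the text should say so.
- The 54 and 66 split has no source beyond the sample-size allowance. If stoppers and missing outcomes coincide, the complaint about the wrong event largely falls away and only the p-value rule remains.
- A condensed article may leave visit-by-visit missing-data tables to a fuller plan. The point here is not that they are absent; it concerns a comparison and a covariate rule that the article itself lays down.

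A reader might infer that the plan gives the MAR assumption no support, that only significant variables enter the model, or that the primary estimate is biased. The documents do not support any of these: missing outcomes are to be explored, the fixed terms carry part of the conditioning, and low power to flag a baseline difference is not in itself bias in the treatment effect.

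**Conclusion.** The point holds in a limited form and is a cheap improvement. The only dropout analysis that the article defines compares by completion of the intervention and so does not target missing UPSA-B outcomes, yet its significant results decide which covariates are added to the primary model. As a selection rule it is weak, with 37% to 77% power for differences of 0.3 to 0.5 SD if 54 of 120 stop, and lower still for predictors of missingness where stopping and missing outcomes overlap only partly. With 10 to 20 independent null variables screened, the chance of at least one spurious inclusion is 40% to 64%. The split, the number of variables and the overlap are assumptions. The likely effect on the primary estimate is modest and may be nil, given the terms already in the model.

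**What to change.** Change three things in the Statistical analysis section.

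1. Base the missing-data comparison on the outcome: baseline values of participants with and without a UPSA-B assessment, at 16 weeks and at 10 months, by arm.
2. Drop the significance-based supplement. Use a fixed covariate list, whatever the p-values, that adds baseline PANSS and the SST/CBT randomisation stratum to the terms already named (site, education, DART, baseline verbal memory, baseline scale values and antipsychotic dose).
3. Keep the comparison of those who leave the intervention with those who complete it, but report it separately as a description of adherence.

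Baseline PANSS and SST/CBT participation are already collected, so no new data are needed. The cost is a change of wording and a few degrees of freedom in the model.

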## Methods

### Randomisation

The NEUROCOM study is a randomised parallel-group clinical trial in which participants are randomly allocated to experimental intervention versus standard intervention (Figure 1**Flowchart of the NEUROCOM trial**. See text for further information.). The centralised, stratified block-randomisation 1:1 is carried out by Copenhagen Trial Unit (CTU) following two stratification criteria: Performance level on UPSA-B (good: total raw score ≥ 16 or poor: total raw score < 16), and participation in OPUS cognitive-behavioral therapy (CBT) group or social skills training (SST) group (yes or no). The generation of allocation sequence is computerised. Allocation concealment is achieved through centralised randomisation with a block-size unknown to investigators.

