A review of cognitive rehabilitation trials underscores the importance of possibilities for individual adjustments [37]. CT is therefore carried out individually with continuous progress evaluation between participant and trainer.

Trainers are occupational therapists and psychologists at bachelor or master level with psychiatric experience. Knowledge has been exchanged throughout the process of the pilot study about cognitive dysfunction in schizophrenia. Trainers were introduced to errorless learning principles, and didactic instruction in the manualised CT has been carried out at meetings during preparation of the NEUROCOM study.

Much empirical research in psychosocial interventions for schizophrenia has shown that training in symptom handling, social proficiency training, and supportive provisions in occupational relations can help patients to function in their daily lives [38-47]. According to Bell et al. [48], there is sufficient evidence that the *combination *of CT and psychosocial treatment, rather than individually occurring initiatives, has the greatest potential for promoting outcome [see also [49,50]]. CT is therefore added to the comprehensive psychosocial programme OPUS.

The OPUS programme consists of affiliation with a primary patient manager, who provides contact on a weekly basis, involves the family, and provides the opportunity for psychoeducation and social skills training [for further details see [51-53]]. Depending on individual needs, patients are offered to take part in group therapy and either social skills training (SST) or cognitive-behavioral therapy (CBT). Participation in SST or CBT can be beneficial for both cognition and everyday functioning. To ensure comparability between the participants in the NEUROCOM trial, we stratify participants according to group therapy (SST/CBT) yes/no before allocation to experimental intervention (CT) versus standard OPUS.

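### The SST/CBT randomisation stratum is not among the listed covariates of the primary UPSA-B model; adding it is a free, minor gain in precision

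*Protocol article*

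**What the plan says.** The Randomisation section names two stratification criteria: UPSA-B raw score at or above 16 versus below 16, and "participation in OPUS cognitive-behavioral therapy (CBT) group or social skills training (SST) group (yes or no". Both are reported to the trial unit when a randomisation is requested.

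The Experimental intervention section gives the reason for the second: "Participation in SST or CBT can be beneficial for both cognition and everyday functioning". To keep participants comparable, "we stratify participants according to group therapy (SST/CBT) yes/no before allocation to experimental intervention (CT) versus standard OPUS".

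The Statistical analysis section then lists what goes into the repeated-measurements model for UPSA-B:

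- the baseline outcome: "In this model, baseline values of the scales are included";
- the named covariates: "Variables included as covariates will be site (Aarhus/Copenhagen), level of education, pre-psychotic IQ (DART), baseline values of secondary verbal memory";
- a conditional set: "the baseline values of variables that differ significantly in dropout analyses";
- for the analyses in general, antipsychotic dose: "Dosage of antipsychotic medication (in chlorpromazine equivalents) will be included as a covariate variable in the analyses".

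SST/CBT is not named in any of these.

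**The concern.** When randomisation is balanced within a stratum related to the outcome, the difference between strata no longer adds to the sampling variation of the treatment contrast. A model without the stratum still counts that difference as residual noise. Its standard error is therefore larger than the true one, the confidence interval is wider than needed, and the test rejects less often than its nominal level.

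The protocol itself links SST/CBT participation to everyday functioning, which is what the primary outcome measures. It went to the trouble of balancing the factor and then wrote a covariate list that does not use it. What is at stake is some precision and agreement between design and analysis, not the validity of the result.

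**Working it through.** **Text check.** Set the two stratifiers against the model terms.

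| Stratifier | Term in the model that carries it |
|---|---|
| UPSA-B level (16 or more / below 16) | Baseline UPSA-B, which holds more information than the two-level split |
| SST/CBT group (yes/no) | None fixed; enters only if significant in the dropout analysis |

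**Inputs from the document (Sample size estimation).** Difference 1 point, SD 1.66, alpha 0.05, taken here as two-sided. The plan states 31 evaluable per group and recruitment of 60 per group with 45% dropout. 60 × 0.55 = 33, so 32 per arm is used for the evaluable sample and 60 per arm as the limit without dropout.

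**The plan's own figure.** The document gives no figure for the effect of this stratum. Its sample size of 31 per group is not reproduced by the two-sample formula: 2 × (1.66 × (1.96 + 1.2816))² / 1² = 57.9, so 58 per group. Power at 31 per group is about 66%. That is a separate matter. It matters here only because it explains why the baseline power below is near 66% and not 90%.

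**Assumptions, not given in the document.** Strata of equal size, exact balance between arms, no other covariates, and a gap between strata of g residual SD with g = 0.3, 0.5 or 0.8. The total SD is held at 1.66, because the protocol gives that as the SD of the outcome with no stratum removed.

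**Formulas.**

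- Total variance = residual variance × (1 + g²/4). Let k = √(1 + g²/4), so the residual SD is 1.66 / k.
- Share of variance due to the stratum = (g²/4) / (1 + g²/4).
- Without the term, the reported standard error is about k times the true one, so type I error ≈ 2 × (1 − Φ(1.96 k)).
- With the term, the standard error is (1.66 / k) × √(2/n). At n = 32, √(2/32) = 0.25.

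| | g = 0.3 | g = 0.5 | g = 0.8 |
|---|---|---|---|
| k | 1.011 | 1.031 | 1.077 |
| Residual SD (points) | 1.64 | 1.61 | 1.54 |
| Gap (points) | 0.49 | 0.81 | 1.23 |
| Share of variance | 2% | 6% | 14% |
| Standard error with the term, 32 per arm (0.415 without) | 0.410 | 0.403 | 0.385 |
| Type I error without the term: formula | 4.7% | 4.3% | 3.5% |
| Type I error without the term: simulation | 4.5% | 4.3% | 3.4% |
| Power at 32 per arm, without the term (simulation) | 66% | 66% | 67% |
| Power at 32 per arm, with the term | 67% | 68–69% | 72% |
| Gain at 60 per arm, from about 91–92% | 0.3 points | 1 point | 2 points |

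With the term, type I error is about 5% throughout. The small differences between formula and simulation in the type I error rows are within simulation error.

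**Extreme case.** If the strata differed by a full total SD (1.66 points, 25% of the variance), type I error without the term would be about 2.3%. Power at 32 per arm would be 67.8% without the term and 78.3% with it. Nothing in the document suggests a gap that large.

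**The case against.** **The factor may matter little.** The protocol says only that participation may help and gives no association with UPSA-B. Groups are offered according to individual need, so a difference in need could offset any benefit. The planned model already holds baseline UPSA-B, education, IQ, verbal memory and antipsychotic dose. What counts is the variance SST/CBT explains beyond these, and that is unknown. This stands, and it limits the size of the point. A reader might say that the protocol calls the factor prognostic; it does not go that far.

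**There is a route into the model.** SST/CBT participation is recorded at the assessments, and the dropout clause could bring it in. But that makes the use of a design factor depend on a significance test, so it is not a pre-specified term. An unseen analysis plan does not settle it either, because the article states the covariate list itself.

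**Stronger readings that the document does not support.**

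- *Power falls towards 60%.* A reader gets this by adding the stratum gap on top of the SD of 1.66, which raises the total SD above the planning value. With total SD held at 1.66, power without the term stays at 66–67%. The omission forgoes a gain and does not push power below that level.
- *Dropout imbalance biases the result.* With 45% dropout the strata could become unbalanced among those observed, and the extra term would then help. But the document gives no figure from which to judge this, and the calculation above assumes exact balance.
- *Listing site is a mistake because it was not a stratifier.* Adjusting for centre in a two-site trial is sound.
- *The sample-size shortfall makes this point more serious.* That is a separate issue and does not change the size of this one.

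**Conclusion.** The omission is clear from the text: one of the two randomisation strata has no fixed place in the primary model. Its consequence is mild. While balance holds there is no bias and no inflation of type I error, only a somewhat conservative test and some lost precision.

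Over the range g = 0.3 to 0.8, the loss runs from under 1 to about 5 percentage points of power at 32 per arm, and from about 0.3 to 2 points at 60 per arm. These figures assume equal strata, exact balance, a single continuous outcome without other covariates, and total SD 1.66. They are not a simulation of the planned repeated-measurements model, where the gain could be smaller. Confidence is high in the omission and its direction, and low in its exact size. This is a free improvement of minor severity.

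**What to change.** Add SST/CBT group (yes/no) as a fixed covariate in the primary UPSA-B model and in the other outcome models. Keep baseline UPSA-B and site. Name it in the list outright, so that it does not depend on the dropout analysis.

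Use the status reported to the trial unit at randomisation, not participation recorded later. The Discussion expects that cognitive training may reduce participation in OPUS, so later attendance could itself be affected by treatment.

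The cost is about one degree of freedom and no new data. The change should be fixed before the allocation is revealed for analysis.
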